### Adverse events and safety monitoring

Throughout the trial, participants will be monitored on weekly basis to ensure safety. In case of any allergic reactions or adverse events, prognostic treatment will be provided after proper investigation free-of-cost. Further, participants will be encouraged to report to and contact the designated personnel in case of any discomfort or adverse event 24/7 to ensure the reporting and treatment of adverse events within 24 h. The principal investigator will then decide the continuation of the trial treatment after excluding for the factor unrelated to the trial medications. There are no anticipated harms of the interventions of the present trial; therefore, no post-trial care and compensation has been planned for participation in the present trial.

### Strategies for improving adherence

For improving the adherence of the trial, contact numbers of the parents of the participants will be collected, and a daily reminder text/call will be dropped. Empty treatment packets will not be collected for ensuring the blinding of the study. In addition to this, the parents of the participants will be incentivized through multi-vitamins for their other children and family members.

### Outcome parameters

All the assessments will be carried out by a trained staff unrelated to the enrolment and allocation procedures. The primary outcome of the trial is to examine the microbiome diversity of malnourished children, to compare it with healthy children, and to evaluate the effect of RUTF plus prebiotics on the microbiome diversity of malnourished children (Table 3). For achieving the primary outcome, 5 g stool sample of the children will be collected for DNA extraction using QIAamp DNA Stool kit (Qiagen, Hilden, Germany) for examining the microbiome diversity through 16 Svedberg (S) ribosomal ribonucleic acid gene sequencing.

**Table 3 Tab3:** Primary outcome parameter

*Outcome measure*	*Measure description*	*Time frame*
Microbiome diversity	Microbiome diversity examination among malnourished children using 16 Svedberg (S) ribosomal ribonucleic acid gene sequencing. The microbiome diversity index measures the diversity of microbial species in malnourished children’s gut microbiota, comparing it to reference and control populations. Higher values indicate greater diversity, providing insights into malnutrition’s impact on gut microbiota composition	8 weeks

For the accomplishment of secondary outcome parameters, anthropometric measures of the children, including their height, weight (for calculating weight-for-height/length z-score), and MUAC will be assessed by a trained healthcare staff. For assessing neurodevelopment of children, the Malawi Development Assessment Tool (MDAT) will be used that is considered to be one of the most valid tools for assessing child development for ages 0–59 months measuring their motor, language, social, and cognitive development [29], while for assessing the muscle mass accumulation, Body Stat Analyzer will be used (Table 4).

**Table 4 Tab4:** Secondary outcome parameters

*Outcome measures*	*Measure description*	*Time frame*
Anthropometric measurements	Change in the mean weight-for-height/length *z*-score and MUAC in children with complicated severe acute malnutrition who have been taking prebiotics supplementation for 8 weeks	8 weeks
Neurodevelopment assessment	Impact assessment of prebiotic supplementation on children’s neurodevelopment using the Malawi Development Assessment Tool	8 weeks
Muscle mass accumulation	The study investigates the impact of prebiotic consumption on body composition changes using the Body Stat Analyzer as a quantitative measurement tool	8 weeks

Starch to placebo comparator group		x	x	x	x	x	x	x	x	
RUTF plus starch to active comparator group		x	x	x	x	x	x	x	x	
RUTF plus prebiotics to experimental group		x	x	x	x	x	x	x	x	
*Assessments*										
Sociodemographic characteristics	x									
Anthropometric measures (weight, height, MUAC)	x								x	
Fecal samples	x								x	
Malawi Developmental Assessment Tool	x								x	
Body stat analyzer	x								x	
Outcome analysis										x

### Statistical analysis

Intention-to-treat (ITT) analysis will be used in the present trial for analyzing the results. All the participants who are randomized, received at least one intervention, and evaluated for at least one outcome will be analyzed with missing data substituted according to the principle of ITT.

For evaluating the microbiome diversity, Ribosomal Database Project (RDP) Bayesian algorithm will be used to identify microbial structure at phylum and genus level among samples and trial groups using Fast Length Adjustment of Short Reads (FLASH) version 1.2.11 and software R version 3.4.1.

Raw sequence data will be filtered to obtain high-quality clean data with DADA2, after which clean reads that overlapped each other will be merged into tags and clustered to operational taxonomic units (OTU). Taxonomic classifications will be assigned to OTU representative sequences using the RDP database. FLASH version 1.2.11 will be used for generating consensus sequences for paired-end reads, and software R version 3.4.1 will be used to create phylum and genus abundance bar plots. Further, alpha diversity analysis will also be conducted. Alpha diversity is the analysis of species diversity in a sample, measured by observed species index, Chao1 index, Shannon index, Simpson index, and good-coverage index.

Furthermore, Statistical Package for Social Science (SPSS) version 24 will be used for evaluating the change in weight-to-height/length *z*-score, MUAC, neurodevelopment assessment, and muscle mass accumulation among trial participants. Firstly, for descriptive analysis, percentages and frequencies will be presented of qualitative variables (gender of the child, ethnicity, breast feeding history, and mother’s dietary habits), while mean ± SD (in case of normally distributed variables) and median ± inter-quartile range (IQR) (in case of skewed variables) will be given for quantitative variables. Furthermore, the association of the sociodemographic characteristics of the children and mothers with the weight-to-height/length z-score, MUAC, neurodevelopment assessment, and muscle mass accumulation among children will be explored through regression analysis. For comparing the outcomes between three trial groups, test of analysis of variance (ANOVA) will be used with Scheffe and Games-Howell test for post hoc multiple comparisons in case of normally distributed data; otherwise, Kruskal–Wallis test will be applied, while for analyzing the data of repeated measures within the same groups, paired-sample *t*-test (for normally distributed datasets) or will Wilcoxon test (for non-normally distributed datasets) will be applied. All the tests will be applied at 95% confidence interval (CI) by an independent statistician blinded to the study.

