With deficiency of iron recognized in malnourished children [18], galactooligosaccharides (GOS), a form of prebiotic, have been proven to have anti-inflammatory and antimicrobial actions that might enhance response to standard therapy for SAM [22, 23]. These benefits have developed a rising interest in the use of prebiotics in diet to adjust gut microbiome in a way that can improve microbial health [24]. Targeting the gut microbiota through the use of prebiotics as a part of treatment in malnourished children may present an affordable and cost-effective strategy for the prevention and treatment of malnutrition among children as well as in improving their overall health [22]. Prebiotics are considered as a fuel for probiotics bacteria of gut that could protect the host against diarrhea with reduced rates of relapse. However, randomized controlled trials evaluating the effects of prebiotic supplementation on the gut microbiome among children with SAM have not previously been studied. So, there is a gap, as clinical evidence is lacking and the existing knowledge cannot be translated into clinical practice.

Around one trillion organisms per milliliter of luminal contents are found in the distal intestine, where the majority of these bacteria are found [10]. It is essential to describe the microbiota in malnourished children in order to define their potential to harvest energy and nutrients [25]. Therefore, the present study has been designed with the goal to evaluate the effect of prebiotics on the gut microbiome diversity in malnutrition children utilizing a prospective, double-blinded, triple-armed, multi-centered randomized controlled trial. The specific objectives of the present study are to:Examine the role of prebiotics on the microbiome diversity and abundance among malnourished children using 16 Svedberg (S) ribosomal ribonucleic acid gene sequencingInvestigate the role of prebiotics on the anthropometric measures and the body composition of malnourished childrenAssess the impact of prebiotic supplementation on malnourished children’s neurodevelopment

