### Interventions

The detailed dietary intervention that will be provided to the participants recruited to each group is given in Table 2.

**Table 2 Tab2:** Intervention for study groups

*Participant group/arm*	*Intervention/treatment*
Placebo comparator: healthy controls (starch) The healthy controls will be given starch packed in the same way as the active prebiotics	**Dietary supplement: starch only** The starch solution is a low-fat diet **Dosage:** A daily dosage of 4 g of starch mixed with water or milk
Experimental: malnutrition (RUTF plus prebiotics) The malnutrition group with RUTF and prebiotic only. The RUTF will be given as per the WHO guidelines	**Dietary supplement: prebiotic galactooligosaccharide (GOS) Powder** Prebiotic GOS powder is a galactooligosaccharide ingredient low in mono-sugars. Scientific studies have shown positive effects of oligosaccharides, among which GOS, on growth of bifidobacterial, stool consistency bowel function and transit time, support of natural defenses and mineral absorption The product mainly consists of 97% dry matter with 69% prebiotic GOS, 23% lactose, and 5% glucose and galactose as monosaccharides. These prebiotics have β-(4) glycosidic linkages and have been proven as safe product **Dosage:** In this arm, participants will receive a daily dosage of 4 g of prebiotic GOS mixed with milk or water along with RUTF. The dosage of RUTF will be determined based on the weight of the child in such a way that two sachets will be given to a child with a weight of 5–6.9 kg in a day/week, three sachets to a child weighting 7–9.9 kg in a day/week, and four sachets were given to a child with having weight less than or equal to 10 kg in a day/week
Active comparator: malnutrition (RUTF plus starch) The malnutrition group with RUTF and starch only. The RUTF will be given as per the WHO guidelines	**Dietary supplement: RUTF plus starch** RUTF and the starch solution **Dosage:** In this intervention arm of the trial, participants will receive a daily dose of 4 g of starch mixed with milk or water along with RUTF. The dosage of RUTF will be determined based on the weight of the child in such a way that two sachets will be given to a child with a weight of 5–6.9 kg in a day/week, three sachets to a child weighting 7–9.9 kg in a day/week, and four sachets were given to a child with having weight less than or equal to 10 kg in a day/week

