## Discussion

Children suffering from SAM are usually treated with RUTF; however, literature indicates that the iron content present in RUTF may not be sufficient to elevate the iron levels to the optimal range among them [21]. Considering this and the presence of symptoms of diarrhea, pneumonia, acute gastroenteritis, and acute respiratory infections among SAM children, the present trial aims to evaluate the effect of RUTF plus prebiotics on the management and gut microbiome diversity of SAM children. Malnutrition alters the gut microbiome of the children with the gut microbiota of SAM children less diverse as compared to the healthy ones [30]. However, literature highlights the role of prebiotics in stimulating the growth of specific taxa in the gut of the host conferring benefits to their health [31].

Previous studies clearly demonstrate the difference in the diversity of gut microbiome of healthy and malnourished children. Studies indicate a higher relative abundance of Bacteroides in the gut microbiome of children who suffer from diarrhea as compared to those who have recovered from it [32]. Further, the dominance of firmicutes has also been reported in the gut of the healthy host [33]. This is because children who encounter diarrhea at an early age might get impairment in the composition of their gut microbiota, resulting in continuous diarrhea, persistent illness, and underdevelopment [34], whereas GOS, as form of prebiotics, is proven to have positive effects on the growth of beneficial bacteria (including bifidobacterial in the gut), stool consistency, bowel function and transit time, support of natural defenses, and mineral absorption [35, 36]. This indicates that GOS could also provide beneficial results for treating the malnutrition among children by altering their gut microbiome. Likewise, previous trials reveal the beneficial effects of prebiotics on the health of SAM children [22, 37]. However, there is rarely any study that evaluates the role of prebiotics on the gut microbiome of SAM children, to the best of our knowledge.

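### Abundance is half of objective 1, but it is not a listed outcome and is given only descriptive bar plots, and alpha diversity cannot stand in for it

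*Protocol article*

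**What the plan says.** The first specific objective, at the end of the Background, is to "Examine the role of prebiotics on the microbiome diversity and abundance among malnourished children", and the title names the same two targets.

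Table 3 (Outcome parameters) lists one primary outcome, a microbiome diversity index at 8 weeks, with its scale fixed as "Higher values indicate greater diversity". Table 4 lists anthropometry, neurodevelopment and muscle mass. Neither table contains abundance or any taxon.

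In Statistical analysis, the RDP classifier "will be used to identify microbial structure at phylum and genus level among samples and trial groups", and then "software R version 3.4.1 will be used to create phylum and genus abundance bar plots". Alpha diversity is "measured by observed species index, Chao1 index, Shannon index, Simpson index, and good-coverage index". The SPSS paragraph that follows is introduced for weight-for-height z-score, MUAC, neurodevelopment and muscle mass. It then gives ANOVA or Kruskal–Wallis for comparing outcomes across the three groups.

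On mechanism, Table 2 (Interventions) refers to "positive effects of oligosaccharides, among which GOS, on growth of bifidobacterial". The Discussion and the Conclusions repeat the bifidobacterial effect. The Conclusions also expect the prebiotic arm to show improved diversity.

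**The concern.** A bar plot describes. It gives no difference between RUTF plus GOS and RUTF plus starch, no measure of uncertainty and no adjustment for the week-0 sample. An objective about the role of a prebiotic on abundance needs a contrast between the randomised arms, and the published plan does not provide one.

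This matters more here because the mechanism the protocol cites is growth of particular bacteria, while the quantified microbiome measures are whole-community indices. If GOS enriches one genus, an evenness-sensitive index need not rise and may fall. With diversity as the only microbiome result carrying an estimate, a bifidogenic response could be under-reported. Alternatively, a genus could be picked out after the plots have been seen, which would make the claim post hoc.

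**Working it through.** **1. Objective against outcome and analysis**

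| Item | Diversity | Abundance |
|---|---|---|
| Title and objective 1 | yes | yes |
| Table 3 (primary outcome) | yes | no |
| Table 4 (secondary outcomes) | no | no |
| Statistical analysis | five alpha-diversity indices | taxonomic classification; phylum and genus bar plots |

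The ANOVA/Kruskal–Wallis sentence does not close the gap. It sits in the paragraph introduced for the four SPSS variables. Even read broadly, it applies to outcomes, and abundance is not listed as one.

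**2. The plan's own figures**

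The protocol states no figure for abundance, for any taxon or for a diversity index. Its only related number is the sample size. A balanced one-way ANOVA with f = 0.25, three groups and 5% significance has 79.7% power at 52 per group and 80.5% at 53, so the stated 53 reproduces. That calculation is tied to no index or taxon, and this point does not affect it.

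**3. Can alpha diversity stand in for an abundance comparison?**

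Let p be the Bifidobacterium share, and hold the other taxa in fixed proportion to each other, with Shannon index H_rest. The identity is

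H = h(p) + (1 − p) × H_rest, where h(p) = −p ln p − (1 − p) ln(1 − p).

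Setting the derivative ln((1 − p)/p) − H_rest to zero gives a maximum at p = 1/(1 + exp(H_rest)). Above that share, further growth of the genus lowers Shannon.

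The protocol gives neither p nor H_rest, so both are assumed over a range. The values needed are h(0.05) = 0.199, h(0.10) = 0.325, h(0.20) = 0.500, h(0.30) = 0.611 and h(0.40) = 0.673.

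| H_rest (assumed) | Share at which Shannon peaks | Change, 5% to 10% | Change, 10% to 20% | Change, 10% to 30% | Change, 20% to 40% |
|---|---|---|---|---|---|
| 1.5 | 18% | +0.05 | +0.03 | −0.01 | −0.13 |
| 2.0 | 12% | +0.03 | −0.02 | −0.11 | −0.23 |
| 2.5 | 7.6% | 0.00 | −0.07 | −0.21 | −0.33 |
| 3.0 | 4.7% | −0.02 | −0.12 | −0.31 | −0.43 |

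Worked example at H_rest = 2.5, 20% to 40%: 0.500 + 0.8 × 2.5 = 2.50 and 0.673 + 0.6 × 2.5 = 2.17, a change of −0.33.

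Simpson behaves in the same way. With S_rest for the other taxa, S = 1 − p² − (1 − p)² × (1 − S_rest), which peaks at p = (1 − S_rest)/(2 − S_rest). For assumed S_rest of 0.70 to 0.92, the peak lies between 23% and 7%. A rise from 20% to 40% moves Simpson from 0.768 to 0.732 at S_rest = 0.70, and from 0.909 to 0.811 at S_rest = 0.92.

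Observed species and Chao1 measure richness. They need not fall with evenness, but they do not register growth of a genus that is already present. Good's coverage describes how completely the sample was sequenced. None of the five indices identifies a taxon.

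**The case against.** The strongest reply is that this is a condensed article. The choice of a differential-abundance method, the transform and the false-discovery control usually belong in an analysis plan, and one may exist. That is right for the method, and its absence alone would not be a finding. What stands is what this document does fix: an objective that includes abundance, two outcome tables that leave it out, and a stated treatment that stops at plots. An analysis plan normally works from the listed outcomes.

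A reader might go further and infer that bifidobacteria are never compared between arms, or that the trial could not tell an inert prebiotic from one that raises bifidobacteria and lowers evenness. The text does not support that. Classification is planned by trial group as well as by sample, and a genus plot would show a large shift descriptively. What is missing is an estimate with its uncertainty.

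Nor does the plan rest on a single readout that must move the wrong way. Five indices are listed, and the evenness argument does not apply directly to the two richness measures. Table 3 defines the direction of the scale; it does not say that a fall means harm or no effect.

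The mechanism is also wider than one genus. The Discussion speaks of specific taxa and of beneficial bacteria that include bifidobacteria. Bifidobacterium is the natural named target because it is the only one the protocol singles out for GOS, not because the protocol limits the effect to it.

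Finally, the sign of the Shannon change depends on unknown inputs. At H_rest = 1.5, a rise from 10% to 30% changes it by only about −0.01. The protocol describes the SAM gut as less diverse, so low values of H_rest deserve weight.

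**Conclusion.** The point holds as a mismatch between objective, outcome list and analysis. Abundance is promised in the title and objective 1, is not an outcome, and receives only a descriptive display. This conclusion rests on the text and needs no assumption.

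The second part, that alpha diversity cannot stand in for an abundance comparison, also holds, because no listed index measures enrichment of a taxon. How far Shannon or Simpson would mislead is illustrative only. For H_rest between 1.5 and 3.0 and other taxa in fixed proportion, a rise from 20% to 40% lowers Shannon by about 0.13 to 0.43, while smaller rises from a low share leave it flat or slightly higher. Confidence in that consequence is moderate, since the shares and the background diversity are assumed. The planned diversity comparison and the sample size are unaffected. This is a worthwhile, cheap improvement rather than a flaw that invalidates the trial.

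**What to change.** - Add genus-level Bifidobacterium relative abundance at week 8 to Table 4 as a secondary outcome.
- In Statistical analysis, state that it will be compared between RUTF plus GOS and RUTF plus starch, the two randomised arms, on a log-ratio scale (for example centred log-ratio), adjusted for the week-0 value, with an estimate and 95% CI. The healthy group stays as a reference.
- Treat all other genera as exploratory, with false-discovery control. Keep the bar plots as description.
- State that alpha diversity will be interpreted alongside this result, so that a flat or lower Shannon or Simpson index is not read by itself as absence of a prebiotic effect.

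The cost is one outcome line and a few sentences of analysis text. Stool at week 0 and week 8 and genus-level classification are already planned, so no new sample or assay is needed. The downside is one more pre-specified secondary test.

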**Methods:**

The study is designed as a prospective, double-blinded, triple-armed, multi-centered randomized controlled trial, with 6–59 months old uncomplicated SAM children recruited to the experimental group receiving ready-to-use therapeutic food (RUTF) plus prebiotics and the active comparator group receiving RUTF plus starch for 2 months duration (8 weeks). Healthy children with matching age and gender will be recruited to placebo comparator group and will receive starch as a placebo during the study period. A total of 58 participants will be recruited to each arm with 1:1:1 allocation ratio following a pre-defined inclusion and exclusion criteria. The results of the gut microbiome diversity will serve as the primary outcome, while weight-for-height/length *z*-score, mid-upper-arm circumference, neurodevelopment assessment, and body mass accumulation will serve as the secondary outcome. Data collection and evaluations will be conducted at baseline and at the end of the trial (week 8), while the safety monitoring will be conducted at every second week. For analysis, the principles of intention-to-treat will be followed.

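### The primary outcome is defined as one unnamed diversity index but measured by five unranked ones, and one of these, Good's coverage, is not a diversity measure and runs against the stated direction

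*Protocol article*

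**What the plan says.** The abstract of the protocol article fixes the primary outcome: "The results of the gut microbiome diversity will serve as the primary outcome". Table 3, in the Outcome parameters section, treats it as one quantity assessed at 8 weeks: "The microbiome diversity index measures the diversity of microbial species". The index is not named, and the table adds the direction rule "Higher values indicate greater diversity".

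The Sample size estimation section plans for one balanced one-way analysis of variance: three groups, effect size f = 0.25, 5% significance and 80% power, giving 53 children per group.

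The Statistical analysis section covers sequence processing and taxonomic profiling and then adds: "Further, alpha diversity analysis will also be conducted". It describes alpha diversity as species diversity within a sample, "measured by observed species index, Chao1 index, Shannon index, Simpson index, and good-coverage index". No index is singled out. The next paragraph, on the SPSS analyses, says "For comparing the outcomes between three trial groups, test of analysis of variance (ANOVA) will be used", with Scheffe and Games-Howell comparisons after it, and sets a 95% level for all tests. Those post hoc procedures deal with pairs of groups, not with several indices.

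**The concern.** The article describes one primary variable in Table 3 and in the sample size, and five in the analysis. Two problems follow.

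- **Selection.** With five unranked candidates, the index that carries the primary conclusion can be chosen after the results are known. The nominal 5% then no longer describes the chance of a false positive conclusion.
- **Meaning and sign.** Good's coverage appears in the list as a measure of species diversity, which it is not. A reader who applies Table 3's rule to it would call a gut with more rare taxa less diverse. Simpson has the same problem in one of its common forms, and the article does not say which form is meant.

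**Working it through.** **1. The plan's own figure.** Inputs from Sample size estimation: k = 3, f = 0.25, α = 0.05, power 0.80. Power of the balanced one-way F test uses noncentrality λ = k·n·f² with 2 and k(n−1) degrees of freedom. At n = 53, λ = 3 × 53 × 0.0625 = 9.94 with 2 and 156 degrees of freedom, and power is 0.805. At n = 52 power is 0.797. The stated 53 per group is reproduced, for one test of one variable at 5%.

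**2. Direction.** By its standard definition, Good's coverage = 1 − (singletons ÷ reads). For S equally abundant taxa and N reads, the expected number of singletons is N(1 − 1/S)^(N−1). Expected coverage is then 1 − (1 − 1/S)^(N−1), which decreases as S increases.

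A simulation with unequal abundances (lognormal, log-scale SD 2; 5,000 reads; 200 communities per richness level; all assumed values) shows the same. Entries are means.

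| True taxa | Observed | Chao1 | Shannon | Simpson Σp² | Simpson 1−Σp² | Good's coverage |
|---|---|---|---|---|---|---|
| 50 | 46 | 48 | 2.50 | 0.169 | 0.832 | 0.999 |
| 200 | 157 | 177 | 3.59 | 0.078 | 0.922 | 0.995 |
| 800 | 449 | 579 | 4.71 | 0.034 | 0.966 | 0.973 |

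Observed species, Chao1, Shannon and 1−Σp² rise with richness, as Table 3 says. Good's coverage falls, and so does Simpson as Σp².

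**3. False-positive rate if any one index may carry the result.** With m independent tests at 5% the rate is 1 − 0.95^m. For m = 5 it is 1 − 0.774 = 22.6%; for m = 4, with coverage removed, it is 1 − 0.815 = 18.5%.

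The indices are correlated, and the article gives no correlations, so a range was simulated: null data, 53 per arm, a three-group analysis of variance on each index, 20,000 replicates, equal pairwise correlation. The F test is unaffected by reversing an index's sign, so only the strength of a correlation with coverage matters here.

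| Assumed correlation | Five indices | Four indices (no coverage) |
|---|---|---|
| 0.5 | 18.6% | 16.1% |
| 0.7 | 15.7% | 13.8% |
| 0.8 | 13.2% | 11.6% |
| 0.9 | 10.7% | 9.4% |
| 0.95 | 8.6% | 8.4% |

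A two-block pattern (0.9 among observed species, Chao1 and coverage; 0.9 between Shannon and Simpson; 0.5 across blocks) gives 14.3%. One index fixed beforehand gives 5%. Removing coverage alone therefore does not restore 5%.

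**4. Keeping all five as primary.** Bonferroni at 0.05 ÷ 5 = 0.01 per index needs 76 evaluable children per group for 80% power on one index, or 76 ÷ 0.9 = 84.4, so 85 recruited. At 53 per group, power for one index falls to 0.59.

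**The case against.** The strongest reply is that nothing in the article says a positive result on any single index counts as success. The alpha diversity sentence carries no test and no threshold. The paragraph with the analysis of variance opens by listing only secondary outcomes, so its tests reach the five indices by inference. A multiplicity rule is also commonly left to an analysis plan, and one may exist that fixes a single index. This stands: a reader might infer that the trial's error rate is already inflated, but the article does not establish that.

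It does not remove the point. The article itself gives one index in one place and five in another, and its inclusion of Good's coverage among measures of species diversity is an incorrect statement, not an omission.

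Three further readings go too far.

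- A reader might conclude that Table 3's direction rule is wrong altogether. It fails for coverage and, depending on form, for Simpson; it is right for the rest.
- A reader might argue that DADA2 removes singletons and so empties Chao1 and coverage of information. The article says only "Raw sequence data will be filtered to obtain high-quality clean data with DADA2", followed by merging and clustering into operational taxonomic units. Denoising is not named. The argument would also leave fewer than five distinct tests, and coverage cannot be both constant and wrongly signed.
- A reader might want to settle here which groups the primary test should compare. That is a separate matter with its own consequences for power.

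**Conclusion.** The concern holds in a limited form. The primary index is not designated, Table 3 and the Statistical analysis section disagree on whether there is one index or five, and Good's coverage is misclassified, with a direction opposite to the stated rule. These conclusions rest on the article's text and on the definition of coverage at fixed sequencing depth.

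The size of any error inflation is conditional on an any-index reading that the article does not state. Under that reading it is 22.6% at the independent reference and about 9% to 19% for assumed correlations of 0.95 to 0.5. It is 5% if one index is fixed in advance. The sample size is not in error for a single test; it simply presupposes the single primary variable that the analysis section does not name.

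**What to change.** Before unblinding, in the analysis plan, in Table 3 and in the registry entry:

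- Name one alpha diversity index at week 8 as the sole primary measure, with its form and direction. Shannon is one reasonable example; any single index fixed in advance cures the problem.
- Make the other diversity indices secondary, and state Simpson as 1−D.
- Report Good's coverage only as a check of sequencing quality.
- Reword Table 3 so that its direction statement refers to the named index.

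This needs no extra children, visits or samples, and 53 per group still fits one three-group test at 5%. The cost is giving up the choice among indices. If the sponsor prefers several primary indices, a multiplicity procedure and a recalculated sample size are needed; for all five under Bonferroni that is the 76 evaluable per group shown above.
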